### Statistical analysis plan

Data will be analysed using intention to treat analysis for the primary outcome and separate testing with multiplicity adjustments for secondary outcomes. Data will be analysed using SPSS version 25 (IBM, New York) and reported according to the CONSORT statement for RCTs. Descriptive parametric statistics will be presented as percentage for categorical variables and as mean and SD for continuous variables such as age or centiles if the data is skewed. Comparisons between the two groups will be performed with Mann-Whitney U test for independent samples. Subgroups with additional analyses will also be used for detaching outcome differences according to number of home-visits in total, additional medical diagnoses and whether one or two parents participated in the intervention. The level of significance is specified at 0.05. To account for repeated measures, to model within-subject variance, and to handle correlated data of continuous variables a linear mixed model will be used. An interaction term will be introduced in the model to examine heterogeneity effect. For binary and ordinal outcome variables Generalized Estimating Equation (GEE) will be employed. For the main analysis no missing data will be imputed. However, classical multiple imputation methods will be used for an additional sensitivity analysis if any of the included variables has more than 5% missing observations. The GEE is a technique which produces unbiased estimates under the assumption that missing observations will be missing at random. An amended approach of weighted GEE will be employed if missingness is found not to be at random. We will perform residual analysis to assess model assumptions and goodness-of-fit.

Generalized linear modelling will be used for outcome variables that are not repeated to create regression models with distribution of the binary and ordinal dependent variables.

The Bonferroni method will be used to appropriately adjust the overall level of significance for multiple comparisons. Count variables will be analyzed using the Poisson regression model. Qualitative variables from the semi-structured interviews will be analysed for their thematic content. The Pearson chi-square test will be used to detect associations between categorical variables, and the mean and standard deviation will be presented for normally distributed continuous variables.

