### Control group (CG)

The intention of the control condition is that they will receive treatment as usual (TAU). The TAU in Sweden for EPT-born children consists of home-care nursing visits as long as the infant is tube-fed or in need of extra oxygen supply. The recommended basic follow-up for high-risk children in Sweden includes a standardised doctor’s examination at full term, hearing screening and ophthalmologist assessment. At 3 months CA, a physiotherapist and paediatrician assess the infant’s early motor development and neurological progress. Additional follow up visits are common during the first year upon clinical indication. At 1 year CA, the child re-visits the paediatrician and physiotherapist for further motor and neurologic assessment. Throughout the care chain, the paediatrician may refer the patient to the neurologist, pulmonologist, gastroenterologist or child habilitation centre if indicated. At 2 and 5.5 years of age, the child is assessed by a psychologist, paediatrician and physiotherapist. The psychologist assesses the child’s cognitive level and screens for communicative and behavioral problems. The neonatal follow-up team collaborates closely with a speech and language therapist, an occupational therapist and a dietician, all of whom may join the team assessment if necessary. Concerning the SPIBI control group, the recruitment process implies approximately three coordinator visits, four baseline questionnaires of the parents and one extra child physiotherapy assessment. All study participants, controls and intervention children will receive an extended follow-up programme, with additional assessment and questionnaires at term age, 3 months corrected age, 12 months corrected age, 24 months corrected age and 36 months corrected age. In addition, all EPT children in Stockholm are offered a standard follow-up programme and will be referred to specialized care when needed.

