### Trial design

The SPIBI trial is a two-arm randomized trial with four recruiting sites in Stockholm. The intervention group (IG) receives 10 visits and two telephone calls from a special trained interventionist (see Table 3). The focus of the intervention is providing strengths-based support of the parent-child interaction, sensitizing parents to infant cues, helping the parent to give optimal developmental support to the infant and enhancing the infant’s self-regulating skills. All extremely preterm children in Stockholm are routinely offered an extensive follow-up test programme, and SPIBI participants are subject to additional assessments at 3 months, 12 months, and 24 months corrected age. Additionally, the children’s preschool teachers will be interviewed when they reach 36 months corrected age. Control participants will have an additional meeting with the project coordinator when they are informed that they have been allocated to the control group, in which information will be provided about the discharge process, their child’s behavioural cues and the importance of parent-child interaction at home. The trial began on 1 September 2018, and recruitment is anticipated to end on 31 August 2020 or at a later date when the target 130 is reached. The intervention will continue for 1 year after the last participant has been included.

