### Recruitment and randomization

#### Recruitment

The PhD student working with the project spends 8–20 h per week as a project coordinator (see Table 3) visiting the four neonatal units and two medical child wards to identify families eligible for recruitment. The standard procedure for recruitment includes three visits. The first visit takes place during GW 32–36 and aims to provide initial information about the discharge process in general, including the neonatal follow-up programme and the SPIBI project in particular. This initial visit is only implemented if the nurse or neonatologist in charge of the child considers the patient to be medically stable. Two days to three weeks later, a second visit will take place, during which parental questions are answered and the intervention programme as well as the conditions for participating in an RCT are explained in detail. It is stressed that research participation is voluntary and that the family may withdraw from the project at any time with no further consequences. Participating parents are given a three-page information sheet and a consent form to sign, as well as four baseline assessment questionnaires. During the third visit, informed consent and baseline questionnaires are collected, and information about the project is repeated if necessary. The participant is randomized, and if assigned to the control group, a fourth visit is needed to provide information about this circumstance, as well as the fact that the child and parents are now a part of an extended follow-up starting at 3 months corrected age, and at 1 year corrected age, the PhD student will see the family again for assessment and a follow-up interview. If the participant is assigned to the intervention group, the assigned interventionist will visit the family as soon as possible.

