Intervention (s)	Active comparator: Home-based post-discharge intervention for extremely premature infants and their parents. The intervention consists of one hospital visit, nine home-visits and two telephone calls during the first year corrected age, specifically from 1 week before discharge to 12 months corrected age. The intervention is strengths-based working with the infant-parent interaction, supporting infant development and strengthening the parent in his/her role.		
	Control condition: The participants of the Control Group receives treatment as usual, which consists of a regular follow-up program with neurodevelopmental assessment at term age, 3 months corrected age, 12 months corrected age, 24 months corrected age and 66 months corrected age. Compared to children not participating in the study, the control group will receive an extended follow-up program, with assessment and questionnaires at term age, 3 months corrected age, 12 months corrected age, 24 months corrected age and 36 months corrected age. Participants in the control group will be referred to specialized care when needed.		
Key Inclusion and Exclusion Criteria	Inclusion Criteria: • extremely premature born infants • close to discharge from their neonatal intensive care unit hospital stay at Stockholm county council (Stockholms Läns Landsting).		
	Exclusion Criteria: • Children with parent/parents who do not communicate in Swedish or English. • Patients not residing in Stockholm County. • Acute surgery patients who will spend a lot of time at hospitals far from Stockholm		
Study Type	Interventional		
	Study design Method; randomized Masking; Semi-masked, primary outcome assessor is blind to allocation Assignment; Parallel Purpose; The purpose of the SPIBI is to improve parent-child interaction, child development and parental mental health		
	Phase; Not fully applicable, Phase II/Phase III		
Date of First Enrollment	September 2018		
Sample Size	Planned: 130		
	Today (22nd of November 2019): 48		
Recruitment Status	Recruiting		
Primary Outcome (s)	Emotional Availability of parent and child measured with Emotional Availability Scales EAS.		
	Time point: 12 months corrected age		
	Method: Video Observation of 20 min parent-child interaction, assessed with the manualized method of EAS consisting of 4 parent-specific domains and 2 child-specific domains.		

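### Subgroups by number of home visits and by one or two participating parents form after randomisation with no valid control counterpart, so they are not randomised comparisons

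*Protocol article*

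**What the plan says.** The Statistical analysis plan section of the protocol article commits to subgroup analyses: "Subgroups with additional analyses will also be used for detaching outcome differences according to number of home-visits in total, additional medical diagnoses", followed by "whether one or two parents participated in the intervention". The next sentence sets the significance level at 0.05. The section does not call the visit or parent analyses descriptive, and it names no method for handling selection into their levels.

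Other sections show when these two variables arise and for whom:

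- **Trial design:** "The intervention group (IG) receives 10 visits and two telephone calls from a special trained interventionist".
- **Trial summary table, intervention row:** "The intervention consists of one hospital visit, nine home-visits and two telephone calls during the first year corrected age". The contact period ends at 12 months corrected age, which is also the time point of the primary outcome.
- **Recruitment:** consent and baseline questionnaires are collected, the family is randomised, and only then do the interventionist's visits begin: "If the participant is assigned to the intervention group, the assigned interventionist will visit the family as soon as possible".
- **Control group:** controls receive treatment as usual. This includes "home-care nursing visits as long as the infant is tube-fed or in need of extra oxygen supply", but no SPIBI visits.

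**The concern.** A subgroup analysis keeps the protection of randomisation only if the subgroup is fixed before allocation, or cannot be affected by it, and can be identified in both arms. Neither condition holds for the number of SPIBI visits received or for how many parents took part in the intervention.

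The primary outcome is emotional availability, scored from filmed parent-child interaction. Families who keep more appointments, or in which both parents take part, may differ in engagement, stress, household circumstances or the infant's health. Any of these may also affect the score. A gradient across visits could then appear with no treatment effect, or a real one could be masked. The Discussion says positive findings could support wider introduction of the programme, so an apparent benefit of more visits or of two parents could be read as guidance on how to deliver it.

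**Working it through.** **1. The plan's own figure.** Inputs from Sample size and statistical power: 130 participants, half to each arm (65), d = 0.5, alpha 0.05 (two-sided assumed), power 0.8. Normal approximation: 0.5 × √(65/2) = 2.850; 2.850 − 1.960 = 0.890; Φ(0.890) = 0.813. The t-test version gives 0.808. The stated 0.8 reproduces. It concerns the randomised comparison and is not in dispute.

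**2. Does each variable exist before allocation and in both arms?**

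| Variable | Known before allocation? | Defined in controls? |
|---|---|---|
| SPIBI home visits received | No; visits start after allocation and run to 12 months corrected age | No |
| Home visits including usual-care nursing | Mostly not | Yes, but governed by tube feeding or oxygen need |
| One or two parents participating in the intervention | No | No |

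The second row is the most generous reading of a total number of home visits. It supplies a count in both arms, but one that tracks illness severity, so confounding by illness takes the place of confounding by engagement.

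**3. How large could the distortion be?** The documents give no distribution of completed visits and no link between engagement and outcome, so the following inputs are assumptions:

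- no true intervention effect, and 65 families per arm with complete data;
- latent engagement U, standard normal, correlated 0.7 with visits received;
- outcome with SD 1, correlated r with U, where r = 0.1, 0.3 or 0.5;
- the intervention arm split at its median visit level (33 high, 32 low);
- unadjusted t-tests at 0.05, 20,000 simulated trials for each r.

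Expected high-minus-low difference: 2 × √(2/π) × 0.7 × r = 2 × 0.798 × 0.7 × r = 1.117r, that is 0.11, 0.34 and 0.56 SD. Simulation results:

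| r | High − low (SD) | p<0.05 | High − all controls (SD) | p<0.05 | Intention to treat, p<0.05 |
|---|---|---|---|---|---|
| 0.1 | 0.11 | 7% | 0.06 | 6% | 5% |
| 0.3 | 0.33 | 27% | 0.16 | 11% | 5% |
| 0.5 | 0.55 | 63% | 0.27 | 25% | 5% |

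Hand check at r = 0.3: the standard error is √(1/33 + 1/32) = 0.248; 0.33/0.248 = 1.33; Φ(1.33 − 1.96) = Φ(−0.63) = 0.26, in line with 27%.

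The plan does not say which contrast it will use, so two are shown. Bonferroni adjustment would lower the rejection percentages but would leave the shifts in SD units unchanged, because it addresses multiplicity and not selection.

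**The case against.** The strongest reply is that these are additional analyses, that intention to treat is fixed for the primary outcome, and that describing outcome by visits received is an ordinary adherence summary. The first two parts stand and limit the severity: no subgroup result enters the primary comparison. The third would stand if the plan said the analysis was descriptive. As written, it sets out to separate outcome differences by these variables and gives them no such status.

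A reader might infer more than the document supports:

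- **That the planned interaction term cannot be estimated.** The text says only "An interaction term will be introduced in the model to examine heterogeneity effect". The sentence follows the one on the linear mixed model for repeated measures and names no variable. It could mean group by time, or a factor present in both arms. Only if it were meant for visits or participation would it fail.
- **That the diagnosis subgroup has the same defect.** Diagnoses exist in both arms. The article does not say whether only those made before randomisation count, but that is a detail a condensed article may leave to the full plan.
- **That the trial will claim a causal dose-response, or compare high-visit families with all controls.** The section states neither the contrast nor its interpretation.
- **That the bias must favour the intervention.** The illustration assumes engagement raises both visits and outcome. Extra contact for families in difficulty would push the other way.
- **That the spurious gradient equals the assumed effect of 0.5 SD.** This happens only at the top of the assumed range.

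**Conclusion.** The point holds for two of the three named subgroup variables: number of home visits and parental participation in the intervention. Both are determined after randomisation and lack a valid control counterpart, so differences across their levels are not randomised comparisons. This follows from the document's own account of timing and of the control condition, and needs no numerical assumption.

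The size does rest on assumptions. With no true effect, a within-arm visit contrast reaches p<0.05 in roughly 7% to 63% of trials for r from 0.1 to 0.5, given a 0.7 correlation of engagement with visits, a median split and complete data. These figures show what is possible; they do not predict what this trial will find.

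Severity is moderate. The intention-to-treat comparison at 12 months corrected age stands as planned, and the document does not support reading this point as a threat to it.

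**What to change.** 1. **Parent subgroup.** Define it by a variable recorded before randomisation in both arms, for example the number of parents who consented or who completed baseline questionnaires. The Recruitment section has both collected before the family is randomised. Test it by an arm-by-subgroup interaction.
2. **Visits and participation.** Report both as adherence in the intervention arm. Label any within-arm association with outcome descriptive and non-causal.
3. **Optional.** A complier-average analysis with randomisation as the instrument may be added if its assumptions are stated. One is that allocation acts only through the visits, which is open to question: the intervention arm also receives two telephone calls, and controls have an additional coordinator meeting. If visits enter as a graded exposure, linearity is needed as well.

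The cost is a change of wording and an interaction model on data already collected. The downsides are that the parent subgroup would describe availability at baseline and not actual participation, and that no causal claim about the number of visits could be made.

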To improve child development within several areas	Child’s general development (BSID-III, ASQ, SDQ), Child executive function (BRIEF-P), Child’s motor development (AIMS, PDMS, GMA), Child’s neurological development (HINE, HANE), child’s autistic symptoms (M-CHAT), child’s temperament (IBQ-R), preschool teachers view of their extreme preterm pupil (CEQ, “Ert barn vårt samspel”, playtime/social time impression scale, ICF-CY and semi-structured interview with the preschool teachers).	Motor skills assessment will begin at 3 months corrected age at the neonatal follow-up unit. Other child outcomes will be measured at 1, 2 and 3 years corrected age, in accordance with the age range the assessment and questionnaires are applicable for. Preschool teachers’ view of their extreme preterm pupils will be collected at 2 or 3 years corrected age, depending on preschool introduction for that specific child.
Objective 3:		
To improve parental mental health of parents to extreme preterm infants post-discharge	Parental mental health (STAI & HADS) and views of parenthood (PSE & RES).	Parental questionnaires will be collected at baseline and when their child has reached an age of 1, 2 and 3 years corrected age.
Objective 4:		
Collecting parental views of the first year at home after NICU-discharge with an EPT infant; both intervention and control group.	Semi-structured interviews with a focus of the first year at home, strengths and challenges. CSQ from intervention group.	Post intervention at 1 year corrected age.

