### Sample size and statistical power

The hospitals in Stockholm treat more than 100 extremely preterm infants every year, but several of them are not residents of Stockholm County, which is a prerequisite for study inclusion. The study team is prepared to recruit 130 participants, 50% of which will be randomized to the SPIBI intervention. The sample size is based on feasibility, and the assumption is that the effect size of the intervention on the primary outcome measure Emotional Availability Scales (EAS) will be moderate, i.e., Cohen’s d = 0.5. This is largely in line with the results of Flierman et al. [50] for the sensitivity scale of the EAS in the previously mentioned Dutch trial. Hence, we aim to recruit 130 participants, which gives us a power of 0.8 given a normal distribution and an alpha value of 0.05.

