### Outcome measurements

Since the SPIBI is a multi-professional intervention, the outcome is measured across several domains: outcomes concerning emotional availability in the dyadic relation, outcomes measuring child development and outcomes related to parental mental health and parenthood.

The *primary outcome* is the Emotional Availability Scales (EAS) [65], which will be used primarily at 12 months corrected age but then again at 24 months corrected age. The primary coder is blind to group allocation, whereas the second coder, who is used for interrater reliability checks in 20% of the cases, is not. The scale has four parental dimensions (sensitivity, structure, non-intrusiveness, and non-hostility) and two child dimensions (child responsiveness and child involvement). Each subscale has a maximum score of 29 and a direct score of 1–7. It is hypothesized that higher scores will be observed in the intervention group. Previous international studies have shown significant effects of parental sensitivity and structuring as well as child involvement [50], which also seem to be the subscales most indicative of maternal anxiety in the NICU [66].

The *secondary outcome measurements* are listed below. For measuring the cognitive, language, and motor development of the children, the Bayley Scales of Infant and Toddler Development, Third Edition (BSID-III) [67], will be used at 24 months corrected age. Composite scores are standardized to mean (SD) scores of 100 [15], based on age-matched normative data. The secondary hypothesis is that the mean will be higher in the intervention group.

The child’s executive function at 24 and 36 months corrected age will be measured with the Behaviour Rating of Executive Function, Parental Version (BRIEF-P) [68, 69]. All 5 subscales (*inhibit, shift, emotional control, working memory and plan/organize)* will be used, and the hypothesis is that the intervention group will have fewer executive problems reported.

Child’s motor development will be measured by the Alberta Infant Motor Scale (AIMS) [70, 71] at 3 and 12 months corrected age. The range of the AIMS is 0–58 points, with a hypothesis of higher scores for the intervention group.

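### The repeated continuous outcomes, including the primary EAS, fall under both an unadjusted Mann-Whitney test and a linear mixed model, with no rule for which decides

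*Protocol article*

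**What the plan says.** All method statements are in the Statistical analysis plan section of the protocol article.

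- Group comparison: "Comparisons between the two groups will be performed with Mann-Whitney U test for independent samples". The sentence names no outcome or visit. Skewness is mentioned just before it, but only for the choice of descriptive statistics.
- Repeated continuous data: "To account for repeated measures, to model within-subject variance, and to handle correlated data of continuous variables a linear mixed model will be used". No sentence gives this model, or the rank test, the deciding role.
- Other outcome types do get a method of their own: GEE for binary and ordinal variables, Poisson regression for counts. "Generalized linear modelling will be used for outcome variables that are not repeated", and that sentence goes on to speak of binary and ordinal variables.

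Outcome measurements places EAS at 12 and 24 months corrected age, with 12 months primary. It places HADS, STAI, PSE and RES at term age and at 12, 24 and 36 months. Table 1, under Hypotheses, agrees: "Parental questionnaires will be collected at baseline and when their child has reached an age of 1, 2 and 3 years corrected age". According to Recruitment, the four baseline questionnaires are collected at the third visit, together with consent, and the family is then randomised.

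Sample size and statistical power assumes that the effect on EAS "will be moderate, i.e., Cohen’s d = 0.5", and states "a power of 0.8 given a normal distribution and an alpha value of 0.05" for 130 participants, half in each arm.

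**The concern.** For EAS and the four parental scales, two p-values can be produced for the same comparison, both with equal standing in the text. If the choice is left until results are known, the nominal 5% level no longer holds, and for EAS that is the trial's confirmatory result.

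The two methods also estimate different things. The mixed model gives a mean difference with a confidence interval, which can be set against the planned d = 0.5. The rank test compares distributions at one visit and has no place for a covariate. If it decides, the pre-randomisation HADS, STAI, PSE and RES scores go unused in the analysis of those same scales. The sample size is stated to rest on feasibility, so precision from data already in hand is the cheapest available.

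**Working it through.** **Inputs from the protocol article.** 130 participants, 1:1, so 65 per arm; d = 0.5 (stated for EAS only); alpha 0.05, sidedness not stated; power 0.8; seven key secondary outcomes in the registration table; Bonferroni named for multiple comparisons.

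**Assumed, not in the document.** Two-sided testing; correlation rho between a parental scale's baseline and follow-up score, 0.4-0.7; d = 0.5 borrowed for the parental scales as an illustration; a Bonferroni family equal to the seven key secondary outcomes.

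**Step 1: the plan's own figure.** Two-sample t-test, 65 per arm, d = 0.5, two-sided 0.05: power 0.808. The stated 0.8 reproduces. A one-sided test gives 0.886 (normal approximation), so the two-sided reading fits.

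**Step 2: cost of the rank test alone.** On normal data the asymptotic relative efficiency of Mann-Whitney to the t-test is 3/pi = 0.955. The effective size is 65 x 0.955 = 62.1 per arm, and power is 0.789. The loss is 0.808 - 0.789 = 0.019, under 2 points.

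**Step 3: type I error if the better of two results is reported.** Null data, normal, 65 per arm, 20,000 runs, proportion with the smaller p-value below 0.05:

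| Pair of analyses | Assumed rho | Type I error |
|---|---|---|
| Mann-Whitney or t-test, 12 months | any | about 0.06 |
| Mann-Whitney or baseline-adjusted model, 12 months | 0.4 to 0.7 | 0.071 to 0.083 |
| Mann-Whitney at 12 months or arm effect averaged over two visits | 0.4 to 0.7 between visits | 0.078 to 0.070 |

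The middle row applies to the parental scales. The first and third can apply to EAS.

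**Step 4: value of the own-scale baseline for HADS, STAI, PSE and RES.** Adjustment multiplies the variance by 1 - rho², so the standardised effect becomes d / sqrt(1 - rho²).

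| rho | Variance cut | Effect for d = 0.5 | Power, alpha 0.05 | Power, alpha 0.05/7 |
|---|---|---|---|---|
| none | 0% | 0.500 | 0.808 | 0.548 |
| 0.4 | 16% | 0.546 | 0.870 | 0.647 |
| 0.5 | 25% | 0.577 | 0.904 | 0.711 |
| 0.7 | 49% | 0.700 | 0.977 | 0.893 |

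The last column is the more relevant one if Bonferroni covers the seven outcomes (0.05/7 = 0.00714).

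**Step 5: EAS.** There is no baseline EAS, so Step 4 does not apply. Any gain would have to come from other covariates, and the document gives no correlation between them and EAS.

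**The case against.** The strongest reply is that the two methods need not conflict: Mann-Whitney can serve single-visit contrasts and the mixed model the longitudinal questions. That is right, and a reader who infers that they are incompatible goes too far. What stands is that the article never makes that division, and the 12-month EAS comparison fits both descriptions.

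A second reply is that covariate lists and model terms are usually left to a full analysis plan, so their absence from a condensed article is no fault. This also stands. The point does not rest on a missing list. It rests on what the article does fix: two unranked methods for the same endpoints, one of them a group comparison that cannot take a covariate.

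Third, precision on the parental scales is lost only if Mann-Whitney decides. The mixed model could carry the term-age score, although no baseline term is stated. The loss is therefore conditional.

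Three stronger inferences are tempting and unsupported:

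- **That baseline information on the primary outcome is thrown away.** No baseline EAS is measured.
- **That adjusting EAS for baseline anxiety would bring a known gain.** Outcome measurements says of certain EAS subscales only "which also seem to be the subscales most indicative of maternal anxiety in the NICU". The remark is hedged, concerns mothers and some subscales, and comes with no figure.
- **That the rank test itself is costly.** Step 2 shows under 2 points of power on normal data.

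It is also fair to say that a mean difference or d could be derived from the means and SDs that the plan promises for normally distributed variables. The rank test still would not supply its confidence interval.

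**Conclusion.** The point holds as a failure to assign roles. For EAS at 12 months and for HADS, STAI, PSE and RES, the article fixes two analyses and does not say which decides. A choice made after seeing results would raise type I error from 0.05 to about 0.06-0.08: modest, but it touches the primary endpoint.

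The gain in precision is secondary and confined to the four parental scales. Its size depends on an assumed correlation, an effect size borrowed from the EAS assumption, and an assumed Bonferroni family, so the power figures are illustrations and not estimates for this trial. No gain for EAS can be quantified from the document. The stated power of 0.8 is correct and is not in dispute.

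**What to change.** In the Statistical analysis plan section, or in the full analysis plan before any outcome comparison:

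1. Name one deciding analysis for EAS at 12 months: a linear mixed model with arm, visit and arm-by-visit, tested by the arm contrast at 12 months and reported with its confidence interval. Apply it to the EAS dimension or dimensions designated primary. A few prespecified pre-randomisation covariates, such as gestational age at birth, are optional.
2. For HADS, STAI, PSE and RES, use the same model for the follow-up visits with that scale's own baseline score as a covariate.
3. Keep Mann-Whitney as a labelled sensitivity analysis.

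The cost is wording. The four baseline scores are already collected before randomisation, and gestational age at birth is known from the eligibility criteria. The registration table shows 48 of 130 recruited on 22 November 2019 and no results, so at that stage the change could be made before any outcome comparison.
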